### Measurement of outcomes

Interim and outcome assessments are collected by research workers using standardised approaches. All laboratory analyses will be carried out by technicians blind to allocation. The main outcome will be treatment differences between the arms at 24 months, with an interim assessment at 12 months.

#### Primary outcomes

The primary outcomes are change in weight (kg) and physical activity (average number of steps per day) between arms. The same methods of assessment as at baseline will be used.

#### Secondary outcomes

Change in LDL cholesterol and CVD risk score will be assessed. The QRISK2 measurement of CVD risk will be sensitive to changes in weight, cholesterol, blood pressure, diabetes status (HbA1c) and smoking status. The number of fatal and non-fatal CVD events and hospital admissions will be recorded via the Hospital Episodes Statistics database [56].

A secondary physical activity outcome will be the amount of at least moderate physical activity (MVPA) in longer than 10 minute bouts, assessed using the accelerometer output. Changes in dietary habits will be measured via analysis of dietary recall data. Health beliefs and depression at 12 and 24 months will be assessed as measures of mediating processes.

The main perspective for the economic evaluation will be that of the health care system. The EuroQol-5D will be used to generate QALYs for use in the economic analyses [57]. Intervention costs will be calculated, taking into account staff time involved in being trained and delivering interventions, overhead costs and sessions provided. For the group intervention the costs will be apportioned over attendees. Other service use will be measured at baseline, 12 month and 24 month follow-up assessments using an adapted Client Service Receipt Inventory (CSRI) [58]. Costs will be calculated by combining service use data with information on unit costs [59]. Secondary analyses will take into account costs for other agencies and will include lost employment costs.

### Statistical analysis plan

A description of the sample will be presented using means and their standard deviations or counts (proportions). Baseline characteristics of those who were eligible but decline to participate with those who consent to participate and those who dropped out of follow up will be compared with participants who complete the study. Analysis and reporting will be in line with the Consolidated Standards of Reporting Trials (CONSORT) guidelines [60], with primary analyses being on an intention-to-treat basis. The differences in treatment effect between the three arms at 12 and 24 months of this partially nested design will be analysed using mixed-effects models with pre-randomisation values as a covariate [61]. In the linear mixed-model treatment arm, time (as a categorical variable with two levels - 12 and 24 months), the interaction between treatment group and time, borough, ethnicity and the baseline values of the outcome variable are the fixed part of the model. The random parts of the models are GP practice (patients are nested in practices) and therapy group. To account for the partially nested design of the therapy group (only patients within the group therapy are clustered within the same group) an approach which matches the non-parallel data structure will be used [61]. The dependency of the repeated observations of the same subjects at 12 and 24 months and the covariance between the residuals within the lowest level (patients) is to be correlated by using an unstructured covariance pattern model. For the final model the group difference estimates and associated confidence intervals will be reported for 12 (for secondary analyses) and 24 months after randomisation.

The large sample size should ensure that all possible confounding variables are equally distributed between treatment arms. However, in a sensitivity analysis we extend the analyses model of the primary analysis by including baseline variables with substantial imbalance, thought to be important in determining outcome, in the model. The potential baseline variables are age, gender, index of deprivation, education, and marital and smoking status.

The described analyses approach provides valid inferences under the assumption that the missing data mechanism can be ignored (missing at random). Sensitivity of results to missing data will be further assessed by including covariates predictive of missingness in the analyses model, using multiple imputation [62] and exploring the effect of relaxing the missing at random assumption to allow for informative dropout, that is letting missingness also depend on the unobserved value [63].

Health care costs will be compared between the three groups. Given that the data are likely to be skewed, we will use bootstrapping methods to estimate 95% confidence intervals around the mean cost differences. Costs including social care and lost employment will also be compared between the groups. The lost employment costs will be based on days lost from work and average wage rates. However, there is a danger of double-counting between QALYs and lost employment, and therefore the cost-effectiveness analyses will be based on the health service perspective. QALYs will be calculated from the EuroQol-5D administered at baseline, 12 months and 24 months. Area under the curve methods will allow us to calculate the QALY gain over the entire follow-up period. If costs are higher for one group compared to another and QALY gains are greater, we will then construct an incremental cost-effectiveness ratio to show the cost per extra QALY gained. There will be uncertainty around cost and QALY estimates and this will be explored using cost-effectiveness planes generated from 1,000 bootstrapped resamples of the data for each of the three comparisons. Finally, we will generate cost-effectiveness acceptability curves, using the net-benefit approach and bootstrapping, to indicate the probability that any of the three approaches is the most cost-effective for different values placed on a QALY gain. The range of values used will be £0 to 100,000. This includes the threshold that is used by the National Institute for Health and Care Excellence of £20,000 to 30,000. Sensitivity analyses will be carried out around key costs, particularly those for the interventions themselves.

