**Methods/Design:**

Individuals aged between 40 and 74 years in 11 South London Clinical Commissioning Groups who are at high risk of developing CVD (≥20%) in the next 10 years will be recruited. A sample of 1,704 participants will be randomised to receive the enhanced MI intervention, delivered by trained healthy lifestyle facilitators (HLFs), in group or individual formats, in 10 sessions (plus an introductory session) over one year, or usual care. Randomisation will be conducted by King’s College London Clinical Trials Unit and researchers collecting outcome data will be blinded to treatment allocation. At 12-month and 24-month follow-up assessments, primary outcomes will be change in weight and physical activity (average steps per day). Secondary outcomes include changes in low-density lipoprotein cholesterol and CVD risk score. Incidence of CVD events since baseline will be recorded. A process evaluation will be conducted to evaluate factors which impact on delivery, adherence and outcome. An economic evaluation will estimate relative cost-effectiveness of each type of intervention delivery.

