## Methods/Design

### Design

This is a three-arm, parallel, multicentre RCT for people identified as at high risk for CVD. The three arms are usual care, usual care and enhanced MI in a group format and usual care and enhanced MI in an individual format. As participants of the group arm, but not the other two arms, are clustered within groups we have a partially clustered (or nested) design. Simple randomisation will be used, with GP practice included as a random factor in the model, and emphasis being on more practices and fewer patients per practice. The trial is funded by the National Institute for Health Research - Health Technology Assessment Programme (NIHR-HTA) and has been registered with the International Standard Randomised Controlled Trial Number (ISRCTN) registry (identifier: ISRCTN84864870). The study flow chart in Figure 1 shows progression through the study for individual participants.

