#### Fidelity

A fidelity analysis (using mixed methods) will be conducted to assess whether the enhanced MI intervention is delivered according to the manual and to compare whether the level of competencies between the HLFs is associated with variations in outcomes using rating scales and thematic contents analysis of sessions.

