### Sample size

The power calculation of our main outcome variables are based on the findings of previous research [16,36]. We have selected a very conservative effect size of 0.25 expressed as the difference in units of pooled standard deviations, which translates to an ability to detect a difference between two groups of 675 steps per day (physical activity), 1.25 kg weight and 0.25 umol/l total cholesterol at 24 month follow-up. Our study is powered to detect changes which may be modest at the individual level, but would have an important impact if occurring at the population level [37].

We took into account clustering effect within the group intervention (intraclass correlation coefficient = 0.05) by calculating the optimal sample size in presence of differential clustering effects [38]. A sample size of 1,420 participants in total are needed to detect these differences in our primary hypotheses, and a two-tailed alpha of 0.025 to take account of multiple comparisons of the contrasts ‘individual intervention versus control group’, ‘group intervention versus control group’ and ‘group versus individual intervention’. Assuming an approximate dropout rate of 20%, a total sample size of 1,704 (540 in group and 440 in individual and usual care) is needed.

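### The primary model has no facilitator (HLF) random effect, so if outcomes vary by HLF the standard errors against usual care are too small, mainly for the individual arm

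*Protocol article*

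**What the plan says.** The Statistical analysis plan section of the protocol article lists the random part of the primary mixed model in full: "The random parts of the models are GP practice (patients are nested in practices) and therapy group". It justifies the partially nested structure by stating that "only patients within the group therapy are clustered within the same group". Besides treatment arm, time and their interaction, "borough, ethnicity and the baseline values of the outcome variable are the fixed part of the model". No HLF term, fixed or random, appears in this model or in the sensitivity analyses described after it.

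The sample size follows the same view. The Sample size section says "We took into account clustering effect within the group intervention (intraclass correlation coefficient = 0.05") and gives no corresponding allowance for the individual arm.

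The abstract describes the intervention as "delivered by trained healthy lifestyle facilitators (HLFs), in group or individual formats, in 10 sessions". The description of the individual arm says that it has the same components as the group arm, delivered one to one. Under Intervention development, every participant in either intervention arm has an introductory session in which they get to know the HLF. Usual care follows the local Health Check pathway. The Fidelity section plans to "compare whether the level of competencies between the HLFs is associated with variations in outcomes".

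**The concern.** Participants treated by the same facilitator may have correlated outcomes if facilitators differ in effectiveness. The plan recognises treatment-related clustering in one form only, shared therapy-group membership. Participants in the individual arm are treated as independent given their GP practice. Therapy groups are treated as independent of one another even where one HLF leads several of them.

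The terms already in the model do not stand in for HLF. GP practice and borough act identically in all three arms, and there is no arm-by-borough term. They cannot represent variation that exists only among treated patients.

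At stake are the two contrasts with usual care, which are the primary hypotheses. If HLF effects exist, their confidence intervals are too narrow and their type I error exceeds the planned 0.025. The individual arm is the more exposed, because its treatment-related clustering is ignored altogether.

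**Working it through.** **1. Reproducing the plan's sample size.** Inputs from the Sample size section: effect size 0.25 SD, two-sided alpha 0.025 (z = 2.241), ICC 0.05 in the group arm only. Group size is 10 to 11 (Intervention development). Power is not stated; 90% (z = 1.282) reproduces the figure, and 80% and 95% do not.

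- Group-arm design effect with 11 per group: 1 + (11 − 1) × 0.05 = 1.50. The optimal ratio of group to control is √1.50 = 1.225.
- Control n = (2.241 + 1.282)² / 0.25² × (1 + 1.225) = 198.6 × 2.225 ≈ 442.
- Group n = 1.225 × 442 ≈ 541.
- Total = 442 + 442 + 541 = 1,425. With 10 per group the total is 1,403. The plan states 1,420.

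The stated figure is therefore obtained with a design effect of exactly 1 in the individual arm. At 440 v 440 that gives 92.9% power for individual versus usual care. At 540 v 440 with design effect 1.50, group versus usual care has 89.9%.

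**2. Individual versus usual care with HLF clustering.** The number of HLFs, K, and the HLF ICC, ρ, are assumptions. Participants analysed per arm: 440.

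- Design effect DE = 1 + (440/K − 1) × ρ
- True SE / model SE = √((DE + 1)/2)
- Type I error = 2 × [1 − Φ(2.241 / SE ratio)]
- Power = Φ(0.25/√((DE + 1)/440) − 2.241)

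| K | ρ | DE | SE ratio | Type I error | Power |
|---|---|---|---|---|---|
| any | 0 | 1.00 | 1.00 | 0.025 | 92.9% |
| 10 | 0.01 | 1.43 | 1.10 | 0.042 | 86.9% |
| 10 | 0.02 | 1.86 | 1.20 | 0.061 | 80.5% |
| 10 | 0.05 | 3.15 | 1.44 | 0.120 | 63.0% |
| 12 | 0.02 | 1.71 | 1.16 | 0.054 | 82.7% |
| 20 | 0.01 | 1.21 | 1.05 | 0.033 | 90.1% |
| 20 | 0.02 | 1.42 | 1.10 | 0.042 | 87.1% |
| 20 | 0.05 | 2.05 | 1.24 | 0.070 | 77.7% |
| 30 | 0.01 | 1.14 | 1.03 | 0.030 | 91.1% |

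Using 1,704 × 0.3 × 0.8 = 409 per arm instead of 440 changes little. The case of 12 HLFs and ρ = 0.02 then gives SE ratio 1.15 and type I error 0.052. Power here ignores the gain from baseline adjustment, so the comparison with 92.9% matters more than the absolute level.

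**3. Group versus usual care.** Hold the total within-group ICC at the plan's 0.05 and let ρ be the part due to HLF. Then DE = 1.50 + (540/K − 11) × ρ, compared with 1.50 in the planned model. The SE ratio is √[(DE/540 + 1/440) / (1.50/540 + 1/440)].

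| K | ρ | DE | SE ratio | Type I error | Power |
|---|---|---|---|---|---|
| 10 | 0.01 | 1.93 | 1.08 | 0.037 | 84.8% |
| 10 | 0.02 | 2.36 | 1.15 | 0.051 | 79.6% |
| 10 | 0.05 | 3.65 | 1.34 | 0.094 | 65.1% |
| 20 | 0.01 | 1.66 | 1.03 | 0.029 | 88.1% |
| 20 | 0.05 | 2.30 | 1.14 | 0.049 | 80.3% |

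**4. Do the practice and borough terms absorb the effect?** Individual versus usual care was simulated with 4,000 runs per setting. The simulation assumed 120 practices nested in HLFs and a practice ICC of 0.02. The fitted model kept a practice random intercept and borough fixed effects.

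| HLFs | HLF ICC | SE ratio | Rejection at nominal 0.025 |
|---|---|---|---|
| 11 | 0 | 1.01 | 0.024 |
| 11 | 0.01 | 1.11 | 0.043 |
| 11 | 0.02 | 1.20 | 0.062 |
| 11 | 0.05 | 1.42 | 0.117 |
| 20 | 0.01 | 1.07 | 0.034 |
| 20 | 0.02 | 1.10 | 0.038 |
| 20 | 0.05 | 1.26 | 0.075 |

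Under these assumptions the existing terms leave the understatement essentially intact.

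**The case against.** The strongest reply is that the effect is conditional. With an HLF ICC of zero there is no understatement, and the article supplies neither that ICC nor the number of HLFs. The Fidelity section asks whether outcomes vary with competency; it does not say that they will. If the intervention has no effect on anyone, HLF variance is also zero and type I error stays nominal. The inflated rates describe an effect that averages zero but differs across HLFs, with HLFs regarded as a sample from a wider pool. All of this stands, so the point must be worded conditionally.

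The upper end of the range is also weakly supported. The plan's 0.05 refers to therapy groups, where peers interact; participants treated one to one do not. HLFs work to a curriculum, must reach a set competency level and are supervised, and the main assessment comes a year after the last session. These are reasons to give the middle of the range more weight than the worst corner. They do not justify fixing the variance at zero.

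Two stronger readings are tempting. A reader might infer that group versus individual is also distorted, because only one arm carries a clustering term. The documents do not support this. Therapy groups exist only in the group arm, so a penalty there alone is correct, and if the same HLFs serve both arms their effects may partly cancel. A reader might also take the Design section to be wrong where it says "As participants of the group arm, but not the other two arms, are clustered within groups". That statement is true as it stands; it simply does not mention facilitators.

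Finally, the article does not say that one pool of HLFs serves both arms, that an HLF leads several groups, or that a participant keeps the same HLF throughout. The group-arm point depends on shared leadership. The individual-arm point needs only that HLFs each treat several participants.

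**Conclusion.** The concern holds in conditional form. The model's random part is explicitly listed, so this is something the article fixes, not a detail left to a fuller plan. Only the direction is certain: if outcomes vary by HLF, the SEs against usual care are too small.

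For individual versus usual care, with an assumed 10 to 20 HLFs and ICC of 0.01 to 0.05, the true SE is about 5% to 44% larger than the model's, and type I error is about 0.03 to 0.12. A reasonable middle case (12 HLFs, ICC 0.02) gives about 15% and 0.05. For group versus usual care the therapy-group term takes up part of the effect, and the excess is about 3% to 34% over the same range. The sample size contains no allowance for HLF clustering in the individual arm. No conclusion is drawn about group versus individual. The change should be made, but the documents do not show that the planned analysis is invalid.

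**What to change.** In the Statistical analysis plan section, extend the partially nested model with an HLF random effect that is active in both intervention arms and zero in usual care. Nest therapy group within HLF where one HLF leads a group. Use Kenward-Roger or Satterthwaite degrees of freedom and report the estimated HLF ICC. In the Sample size section, state that the calculation assumes no HLF clustering in the individual arm.

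This is a small extension of a model that the plan already adopts. It needs the HLF recorded for each treated participant, which the planned competency analysis appears to require as well. The cost is somewhat wider intervals if HLF effects exist, and an imprecise variance component if HLFs are few. Fitting the HLF term only as a sensitivity analysis would be a weaker alternative, because the primary intervals would still rest on zero HLF variance.

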### Qualitative analysis

The overall aim is to identify and describe factors and processes that affect the delivery, receipt and outcome of the study to aid the interpretation and translation of the observed findings. Process data will be analysed before outcome data wherever possible to reduce bias in interpretation. The main themes will be reach, quality (fidelity) and processes of change.

#### Reach

The extent to which the intervention reached out to eligible participants will be assessed by comparing the reasons given by GPs as to why they agree or decline to participate. We will also assess participation and attrition biases; some patients who have declined to participate in the RCT may be willing to give written informed consent to collect baseline data. We will also invite patients who complete less than 50% of sessions to attend a focus group to give feedback on the programme.

#### Quality (fidelity)

We will measure adherence and competence. Adherence is the extent to which the therapist applies the techniques prescribed in the manual and avoids those proscribed. For MI we will use the MI Treatment Integrity (MITI), which counts the number of MI techniques used [52], and for an overall assessment of competency we will adapt emerging competency frameworks [53-55]. There is no consensus as to the number and order of sessions that should be analysed [25]. Considering the potential massive volume of material we will audiotape sections of 25% of all sessions, selected randomly.

#### Processes of change

We will scan copies of self-monitoring worksheets to measure adherence to the intervention. Supervision checklists and interviews with health trainers will be used to assess which behavior change techniques are popular, why and for which lifestyle behaviour. We will administer a detailed process questionnaire at 15 months that requires all randomised participants to discuss, in open-ended and standardised structured questionnaires, which techniques they had found most useful, their appraisal of the techniques and their level of satisfaction with the interventions of their allocated arms. We will include the usual care arm in order to assess the similarity and differences with the intervention as there may be some overlap.

### Ethical issues

The trial has been reviewed by the Dulwich Ethics Committee and has been approved (reference: 12/LO/0917). The Trial Steering Committee (TSC) will provide overall trial supervision supported by the Data Monitoring and Ethics Committee (DMEC). [name], Professor of Primary Care of the Elderly, University College London is the chairperson for the TSC and [name], Head of International Epidemiology, London School of Hygiene and Tropical Medicine, is the chairperson for the DMEC. The main ethical consideration is to ensure that the risk of harm to participants is minimised and that they are fully informed of any risks. We will take into account literacy and cultural sensitivities in obtaining informed consent. Other ethical considerations are ensuring that recruitment and informed consent are handled in such a way that potential participants are not put under pressure to take part, and that confidentiality is preserved. All participant data will be stored using a unique study identifier and electronic data will be password protected.

In general, regular physical activity is associated with improved health outcomes and this outweighs the risk of sedentary lifestyles. However, a sudden increase in vigorous physical activity in otherwise sedentary individuals is associated with a higher risk of myocardial infarction and of musculoskeletal injuries, which may be pertinent as we are intervening in a group that is at high risk for CVD. However, one of the components of behaviour change techniques is to deliver the message that physical activity should be increased in a graded manner rather than suddenly. We will be discouraging excessive and/or sudden changes to lifestyles. Weight loss could worsen frailty by accelerating the usual age-related loss of muscle that leads to sarcopenia, but combining weight loss with increased physical activity can actually ameliorate frailty [64]. Importantly, our intervention is based on healthier diets and gradual and sustainable weight loss as opposed to commercial weight loss programmes. We consider risks to be small and minimal due to the exclusion of subjects with existing CVD.

